#### 8.1.2.1. Daily walking

"Absolute target" will be calculated as a minimum of a 40% increase from the baseline. This will be calculated as the average of the weekly step count at run-in-phase. Step counts will be monitored using Garmin vivofit 4 band from randomization. Participants will be advised to use the "absolute target" as the minimum reference step count, but try to increase the step count beyond this. Women will be encouraged to perform walking at as speed faster than usual but within the individual's comfort.

Compliance will be calculated based on average step count achieved over a 7-day period including two weekend days. Women achieving at least 80% of the absolute target on a 7-day average will be considered as compliant. Non-compliant participants will be continually motivated and encouraged to achieve their absolute targets either telephonically or by home visits by field workers.

| Baseline
a | 40% increase
b | Minimum
absolute target
(a+b) | 80% of absolute target
(d=a+b) increase
(expected average 1
week step count to be
achieved)
Used to calculate
compliance |
|---------------|-------------------|-------------------------------------|--------------------------------------------------------------------------------------------------------------------------------------------|
| 2500          | 1000              | 3500                                | 3300                                                                                                                                       |
| 3000          | 1200              | 4200                                | 3960                                                                                                                                       |
| 3500          | 1400              | 4900                                | 4620                                                                                                                                       |
| 4000          | 1600              | 5600                                | 5280                                                                                                                                       |
| 4500          | 1800              | 6300                                | 5940                                                                                                                                       |

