| 5000          | 2000              | 7000                                | 6600                                                                                                                                       |
| 5500          | 2200              | 7700                                | 7260                                                                                                                                       |
| 6000          | 2400              | 8400                                | 7920                                                                                                                                       |
| 6500          | 2600              | 9100                                | 8580                                                                                                                                       |
| 7000          | 2800              | 9800                                | 9240                                                                                                                                       |
| 7500          | 3000              | 10500                               | 9900                                                                                                                                       |
| 8000          | 3200              | 11200                               | 10560                                                                                                                                      |
| 8500          | 3400              | 11900                               | 11220                                                                                                                                      |
| 9000          | 3600              | 12600                               | 11880                                                                                                                                      |

For example, if baseline activity is 6,000 steps, then an increase of 40% would be an increase of 2,400 steps a day and absolute target to be achieved/day would be a minimum of 8,400 steps.

Date and version No: 18th July 2019, Version 4.2

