## 10. STATISTICS AND ANALYSIS

### 10.1. Description of Statistical Methods

We will analyse the study using both (1) the intention-to-treat principle and (2) per protocol, including only those participants adhering to at least 75% of the proposed intervention. In addition, we will run a sensitivity analysis to assess the effect of protocol deviation compared to 100% adherence. Analyses will be performed blinded to the intervention group allocation.

Date and version No: 18th July 2019, Version 4.2

Descriptive analysis of the first 40 participants who complete visit 2 (26-28 weeks) will be performed as advised by the funders (MRC-UK). The analysis is intended to assess feasibility, retention and adherence to all study-related procedures.

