## 10.2. The Number of Participants

The sample size is 1856 high-risk women (928 to be recruited in The Gambia and India). The study was powered to have 80% to detect a 33% reduction in the incidence of GDM, for the main effects of diet and PA, with a family-wise significance level of 5% for a two-sided test (i.e. each effect was tested at a significance level of 2.5%). It was assumed that participants could be pooled across centres (no interaction between interventions and country at the 5% level). The sample size was inflated to allow for a 15% drop out rate in each of the four strata, with drop outs defined as non-compliant participants (i.e. no risk reduction in their incidence of GDM).

The effect sizes for the sample size calculation were:

Prevalence of GDM in high-risk pregnant women: The largest study of GDM women (The HAPO study, 25,505 pregnant women unselected for GDM risk at 15 centres in nine countries) reported a GDM prevalence rate, based on IADPSG criteria, of 17.8% among the general population. In our 'high-risk' population, we assume that the prevalence will be higher than in the HAPO study. Therefore, we have estimated the prevalence of 25% in our study.

Estimated risk reduction: A recent meta-analysis (Song et al. Obesity reviews 2016) has shown that either diet or PA results in 18% (95% CI 5-30%) risk reduction in GDM in general pregnant population and interventions as early as 15 weeks of gestational age was also associated with reduced GDM risk (Relative risk: 0.80, 95%CI 0.66-0.97). Putting all these together, we estimate the risk reduction would be higher (about 1/3, 33%) in this high-risk population. We modelled the GDM percentages in four equal-sized combinations of control (c) and treatment (t) arms as 25% (c-c), 16.75% (c-t and t-c) and 11.2 in t-t group. Therefore, in simple comparisons of one exposure, the percentages will be 20.9% vs 13.0%.

Absence of intervention\*country interaction: In order to pool the participants of both countries, we will be assuming that there are no differences between the participants of both countries. This initial test for a non-significant interaction term (at the 5% level) between each intervention and country was also taken into account in the sample size simulation.

The sample size calculation was performed by simulation (in R version 3.5.2) according to the following algorithm:

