### 12.1. DATA SAFETY MONITORING COMMITTEE (DSMC)

An independent Data Safety Monitoring Committee (DSMC) has been set up to review the progress of the trial and provide feedback to the Trial Steering Committee (TSC).

The DMC will be responsible for reviewing

- (i) general study progress (recruitment, compliance, loss to follow-up)
- (ii) clinical study safety data and assess and/or adjudicate all events of deaths
- (iii) the GDM event rate and key secondary/safety outcomes
- (iv) results of the interim analysis. The DSMC includes the following members (To address: chair of DSMC, Report preparation, confirm meeting timelines).

The DMC will review and analyze, on a regular basis, unblinded safety data throughout the study.

An independent DSMC with members who are independent from the Sponsor and the investigators for the PRIMORDIAL study comprises of experts in clinical trials/epidemiology, biostatistics and obstetrics and include the following members

| Name (Designation)                                               | Address                                                                                             | Email                                                        |
|------------------------------------------------------------------|-----------------------------------------------------------------------------------------------------|--------------------------------------------------------------|
| [name]
(Paediatrician & Postdoctoral Research Fellow) | MRC Unit The Gambia at the London School of Hygiene & Tropical Medicine, Fajara, Banjul, The Gambia | [contact]             |
| [name]
(Biostatistician)                         | MRC-LEU, University of Southampton, UK                                                              | [contact] |

Date and version No: 18th July 2019, Version 4.2

|                                     |                                                                      |                                                                          |
|-------------------------------------|----------------------------------------------------------------------|--------------------------------------------------------------------------|
| [name]
(Obstetrician) | Nuffield Department of
Obstetrics and Gynaecology,
Oxford, UK. | [contact] |

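### Section 8.1.2.1 sets two different step thresholds for physical-activity compliance: 1.12 times baseline in the sentence, 1.32 times baseline in the table

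*Protocol*

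**What the plan says.** Protocol section 8.1.2.1 (Daily walking) defines an absolute target for each woman in the two PA arms: her average step count in the run-in week (a) plus at least 40% of it (b). It then states the compliance rule in words: "Women achieving at least 80% of the absolute target on a 7-day average will be considered as compliant".

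A 14-row table follows, for baselines from 2,500 to 9,000 steps. Its last column is labelled as the one from which compliance is calculated, and its heading reads in part "80% of absolute target (d=a+b) increase". That heading mixes the target (a + b) with the increase (b).

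The rule is used while the trial runs. Section 8.1.2.1 says: "Non-compliant participants will be continually motivated and encouraged to achieve their absolute targets either telephonically or by home visits by field workers". Section 10.1 plans a descriptive review of the first 40 women to complete visit 2: "The analysis is intended to assess feasibility, retention and adherence to all study-related procedures". Section 12.1 lists among the monitoring committee's tasks "general study progress (recruitment, compliance, loss to follow-up".

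**The concern.** One section fixes one quantity twice, with different answers. Taking 80% of the target is not the same as taking 80% of the increase, because the target already contains the whole baseline. A woman who changes nothing is already at 1/1.40 = 71.4% of her target, so the sentence asks for little more than her usual activity. The table asks for most of the prescribed change.

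The protocol does not leave this rule to a later document. It states the rule itself, and field staff in two countries apply it from week to week. If one centre works from the sentence and the other from the table, the same step record counts as compliant in one country and non-compliant in the other. At stake are which women are singled out for encouragement, what a reported compliance rate means, whether the rates of the two centres can be compared, and what any PA analysis restricted to compliant women estimates.

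**Working it through.** **Inputs**, all from section 8.1.2.1: baseline a; increase b = 0.40a; absolute target a + b = 1.40a; compliance fraction 80%. The protocol's worked example is: "if baseline activity is 6,000 steps, then an increase of 40% would be an increase of 2,400 steps a day", with a target of 8,400.

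**Step 1. Reproduce the table.** At a = 6,000 the last column shows 7,920.

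- 80% of the increase added to baseline: 6,000 + 0.80 × 2,400 = 7,920. This matches.
- 80% of the target: 0.80 × 8,400 = 6,720. This does not match.

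The second and third columns (b and a + b) are correct in all 14 rows. The last column equals a + 0.8b in 14 of 14 rows and 0.8(a + b) in none. The table is therefore consistent within itself, and a damaged cell does not explain the mismatch.

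**Step 2. Put both rules on one scale.**

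- Sentence: 0.80 × 1.40a = 1.12a. Share of the prescribed increase: (1.12 − 1.00)/0.40 = 30%.
- Table: a + 0.80 × 0.40a = 1.32a. Share of the prescribed increase: (1.32 − 1.00)/0.40 = 80%. As a share of the target: 1.32/1.40 = 94.3%, not 80%.

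**Step 3. Size of the gap.** 1.32a − 1.12a = 0.20a.

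| Baseline a | Target 1.40a | Sentence 1.12a | Table 1.32a | Gap (steps/day) |
|---|---|---|---|---|
| 2,500 | 3,500 | 2,800 | 3,300 | 500 |
| 6,000 | 8,400 | 6,720 | 7,920 | 1,200 |
| 9,000 | 12,600 | 10,080 | 11,880 | 1,800 |

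**Step 4. Who is classified differently.** Every woman whose 7-day average is at least 1.12a but below 1.32a. With a baseline of 6,000 and an average of 7,200 (1.20a), a woman passes by the sentence and fails by the table. The rule applies to two of four equal arms, 1,856 × 2/4 = 928 women on the section 10.2 total. The protocol gives no distribution of achieved steps, so the number who would fall in the band is unknown.

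**The case against.** The best defence is that the intended rule can be inferred. The table gives ready-made thresholds, its heading contains the word increase, and the column is the one marked for judging compliance. The sentence seems simply to have lost that word. The amendment history entry for version 3.0 also puts the 80% on the increase. That entry is superseded text and not evidence of an error, but it points the same way. This stands as a guide to which version to keep. It does not remove the contradiction, because the sentence is current, unambiguous on its own, and the version a reader is most likely to cite.

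The practical effect is also limited. Section 5 provides weekly contact with every participant, covering compliance and motivation. Women are urged towards the same target of 1.40a under either rule. The first-40 review is descriptive, and no stopping or sample-size rule depends on compliance. All of this is right, and it keeps the point modest.

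Two stronger readings are tempting and should be resisted.

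- A reader might infer that section 10.1 adds a third, conflicting threshold, since its second analysis is "per protocol, including only those participants adhering to at least 75% of the proposed intervention". That cut-off covers both interventions and does not mention steps. It can coexist with a weekly 80% rule, for example as a share of compliant weeks, and a statistical analysis plan may define it.
- A reader might infer a loss of power, since section 10.2 allows for 15% drop-out "with drop outs defined as non-compliant participants (i.e. no risk reduction in their incidence of GDM". Nothing there refers to the step rule, and nothing says that observed step compliance will be compared with the 15%. A woman in the disputed band has raised her steps by 12% to 32%, so she is not evidently the zero-benefit woman of that model.

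**Conclusion.** The inconsistency is definite. The sentence sets PA compliance at 1.12 times baseline and the table at 1.32 times baseline, a difference of 0.20 times baseline in every row. In terms of the prescribed increase, that is 30% against 80%. The finding rests only on the protocol's own arithmetic and needs no outside assumption. The table is probably what was meant, but that is an inference from its heading and consistency.

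The effect is on classifying women as compliant during the trial, on the compliance rates in the first-40 review and the monitoring committee's reports, and on any adherence-based PA analysis built on this rule. The documents do not support extending it to the intention-to-treat estimate, the PA target or the sample size. It should be corrected because the rule is in operational use, not because the main result is at risk.

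**What to change.** In section 8.1.2.1 keep the table and replace the sentence with wording such as: *A woman is compliant if her 7-day average step count is at least baseline plus 80% of the 40% increase (1.32 × baseline, last column of the table).* Label that column a + 0.8b. Apply this one rule at both centres, in the first-40 review and in all compliance reports to the monitoring committee.

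If the investigators did intend 1.12 times baseline, the column should instead be recomputed as 0.8(a + b). They would then be accepting 30% of the prescribed increase as compliance.

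As an optional clarification, section 10.1 or the analysis plan could say how the 75% applies to PA, for example as the share of weeks in which the woman was compliant.

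The cost is one sentence and one column label, plus a note to field staff. Section 11.3 already has band data downloaded weekly, so no new data or procedures are needed, and any compliance rates already produced can be recalculated from the recorded steps.

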## 9. SAFETY REPORTING

Safety evaluations will be performed on all randomized participants at each follow-up visit (Visit 1-3). All AE and SAE, including expected SAEs will be captured in the AE report form. The participants will be instructed to contact the study team if there are any concerns regarding the interventions.

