|  | 
intervention (yoghurt and PA) on adverse maternal and new-born outcomes.
               | 
delivery (elective and emergency) captured on delivery records by treating obstetrician
 
 
• Post-partum haemorrhage (Primary) as captured on delivery records by treating obstetrician
 
• Pre-eclampsia and eclampsia based on blood pressure recording at each visit
 
• Blood loss at delivery as captured on delivery records by treating obstetrician
 
 
New born outcomes
 
 
• Pre-term births (<37 weeks of gestational age) calculated from the ultrasound derived gestational age captured at screening visit dating scan.
 
• Foetal macrosomia (defined as birth weight >2 SDs above the population-specific mean in each setting)
 
• Birth weight and length
 
• APGAR score at 1 and 5min of after birth
 
 |
|  | 
(iii) To determine social and cultural barriers to life-style changes during pregnancy
 | 
Questionnaire based assessment of social and cultural barriers.
                                                                                                                                                                                                                                                                                                                                                                                                                                                                                                                                                                                                                                                                                                                                                                                                                  |

Date and version No: 18th July 2019, Version 4.2**2. ABBREVIATIONS**

|        |                                                                      |
|--------|----------------------------------------------------------------------|
| AC     | Abdominal circumference                                              |
| ACOG   | American College of Obstetrics and Gynaecology                       |
| AE     | Adverse event                                                        |
| AFVI   | Amniotic Fluid Volume Index                                          |

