exact equivalents to new born measurements. Therefore, a last trimester scan is essential as it reflects foetal growth more precisely).

- (vii) **Delivery visit:** This is a post-trial surveillance visit primarily intended to assess the safety and efficacy of interventions on pregnancy and new-born outcomes.

Aside from the scheduled study visits, participants will be contacted on a weekly basis either over telephone or visited at home by research personnel. This will be made to ensure general well-being, compliance (wearing device, adhering to individually advised increment in step count, reminders of study visits, yoghurt consumption etc) and motivation.

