| Visit 3 (32 weeks)
End of Study visit      | Weight
Blood pressure
Routine antenatal examination (fundal height)
Fasting plasma glucose
Ultrasound scan (to monitor foetal growth)
Barriers to pregnancy interventions assessment-2 (for future studies)                                                      |
| Delivery
(post-trial surveillance)         | Weight (mother)
Blood pressure (mother)
Intrapartum outcomes
Neonatal outcomes (Birth length, Birth weight, APGAR score)                                                                                                                                               |
| Telephonic contacts / Home visits              | General well-being
Compliance with interventions (step count from accelerometer, yoghurt pot-count)                                                                                                                                                                          |

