### 7.6.4. Post-intervention surveillance visit

All study-related intervention will be stopped at 32 weeks and mother and new born data will be collected during delivery as a part of post- trial surveillance visit. Women who consent will have weekly telephonic contacts/home visits by field staff to ensure general wellbeing. All women will be delivered in the hospital and inter-partum and neonatal measurements will be recorded as below

- I. **Weight of the mother** before delivery of the baby
- II. **Intrapartum maternal outcome assessment**
- III. **Birth length (new born)** The measurement from the crown to the soles of the feet in centimetre scale would be recorded as birth length by an experienced mid-wife.
- IV. **Birth weight (new born)** Weight at birth would be measured within 48 hours of delivery using a calibrated scale for measuring neonatal birth weight by an experienced mid-wife.
- V. **APGAR score (new born)** The APGAR Score should be used as the accepted and convenient method for reporting the status of the new born immediately after birth and the response to resuscitation if needed. Local neonatal practices should be followed for APGAR score reporting in cases of maternal sedation or anaesthesia, congenital malformations and birth trauma. The APGAR assessment would be made as below by a trained medical neonatologist/paediatrician or midwife at 1 and 5 minutes.

Date and version No: 18th July 2019, Version 4.2

| Sign                | 0            | 1            | 2                        |
|---------------------|--------------|--------------|--------------------------|
| Colour              | Blue or Pale | Acrocyanotic | Pink                     |
| Heart rate          | Absent       | <100/minute  | >100/minute              |
| Reflex irritability | No response  | Grimace      | Cry or Active withdrawal |
| Muscle tone         | Limp         | Some flexion | Active motion            |
| Respiration         | Absent       | Weak Cry     | Good, Crying             |

All women recruited in the study will be regularly contacted over telephone or by home visit to monitor general well-being, diet and PA adherence and early detection of serious adverse events and safety to interventions. The additional weekly phone review is also expected to assist with adherence and retention.

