### 7.11. Definition of End of Study

End of study will be the last scheduled visit as per protocol i.e., visit 3 (week 32). However, if the participant chooses to discontinue from the study due to any reasons as stated above in 7.8, the “study termination form” should be completed.

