### 9.2. Definition of Serious Adverse Events

An untoward medical event leading to /resulting in any of the following will be considered as "serious adverse event"

- Death
- is life-threatening
- requires inpatient hospitalisation or prolongation of existing hospitalisation
- results in persistent or significant disability/incapacity
- loss of foetal movements or ultrasonographically confirmed foetal death
- 'Important medical events' if they jeopardise the participant or require an intervention to prevent one of the above consequences.

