#### **11.6. Data preservation strategy and standards**

At the end of the study (when the last participant enrolled in the study completes the delivery visit) the database will be locked and all the electronic study data will be housed in the REDCap Database server until the first publication is made following which the data will be sent to the electronic data archives for long-term preservation. The locked database will have very highly controlled access as detailed in the Archives Research Records Management Policy ([POL-ARM-001](#) - Available on request). All electronic records will be kept indefinitely and all paper records and lab books will be stored in the on-site temperature and pest controlled MRC as dictated by the MRC Unit The Gambia's SOPs on Data Retention and Destruction ([SOP-ARM-005](#)) and formal information/data security standards. The study will be run in compliance with the [MRC Corporate Information security Policy](#) and the MRC Unit The Gambia's INFORMATION AND COMMUNICATION TECHNOLOGY SECURITY [POL-INT-001](#) available on the MRC Gambia intranet (Available on request).

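### New-born safety is an objective, but no adverse-event check is listed at delivery and stillbirth and neonatal death are not named outcomes, so their capture after week 32 is unreliable

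*Protocol*

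**What the plan says.** **Purpose.** Objective (ii) under trial and post-trial surveillance in the Synopsis concerns the safety and efficacy of the lifestyle "intervention (yoghurt and PA) on adverse maternal and new-born outcomes". Section 5 says of the delivery visit: "This is a post-trial surveillance visit primarily intended to assess the safety and efficacy of interventions on pregnancy and new-born outcomes".

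**Safety schedule.** Section 9 states: "Safety evaluations will be performed on all randomized participants at each follow-up visit (Visit 1-3". Section 9.1 has AEs collected at scheduled visits, by field workers at home visits and through weekly phone reviews, and gives no end date. Sections 7.6.1 to 7.6.3 each list a safety assessment. Section 7.6.4, which covers delivery, lists none.

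**New-born items.** The delivery row of the section 7 table gives: "Neonatal outcomes (Birth length, Birth weight, APGAR score". The Synopsis and section 4 add preterm birth and macrosomia.

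**Contacts after week 32.** Section 7.6.4 says: "Women who consent will have weekly telephonic contacts/home visits by field staff to ensure general wellbeing". The last paragraph of the same section has every recruited woman contacted, with early SAE detection among the aims and no end date.

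**SAE definition.** Section 9.2 lists death, without saying whose, and separately "loss of foetal movements or ultrasonographically confirmed foetal death".

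**End of study.** Section 7.11: "End of study will be the last scheduled visit as per protocol i.e., visit 3 (week 32". Section 11.6 places it instead at the point "when the last participant enrolled in the study completes the delivery visit".

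**The concern.** A trial that sets out to judge whether its interventions are safe for the new-born should say who is asked about adverse events up to birth, and should name foetal and neonatal death among the outcomes it compares. This protocol does neither clearly.

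Two planned analyses depend on it. Section 10.3.3 summarises AE and SAE incidence by intervention group, and section 10.3.2 compares intrapartum and neonatal outcomes between groups. The trial is open-label. If ascertainment after week 32 depends on who agrees to be contacted, or on which of two conflicting sentences a site follows, it may differ between arms or between the two centres. Without a count of deaths by arm, a reader also cannot judge whether the APGAR, weight and length comparisons cover all babies or a selected set.

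Section 9.2.1 names events such as preterm labour, membrane rupture, reduced foetal movement and pre-eclampsia as possibly linked to the interventions. All of them can occur between week 32 and birth.

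**Working it through.** The protocol gives no figure to reproduce here. The check sets its sections against each other and adds one piece of calendar arithmetic.

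**1. Is delivery a safety-assessment point?**
- Section 5: yes, by purpose.
- Section 9: safety evaluation is tied to Visits 1 to 3.
- Section 9.1: AEs are collected at scheduled visits. Section 7.11 makes Visit 3 the last of these, although section 5 includes delivery in its visit list.
- Sections 7.6.1, 7.6.2 and 7.6.3: each has a safety-assessment item. Section 7.6.4 has none.
- The section 7 table and Appendix C do not settle it, since neither carries an AE/SAE entry for any visit.

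Result: the stated purpose and the listed procedures do not match.

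**2. Who is contacted after week 32?** One sentence of section 7.6.4 limits weekly contact to consenting women and gives general wellbeing as its aim. A later sentence covers every recruited woman and includes SAE detection. Both cannot govern the same period.

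**3. When does the study end?** Section 7.11 says week 32 and section 11.6 says the last delivery visit. The two may have been written for different uses (participant completion and database lock), but neither says so, and no section states when AE/SAE collection stops.

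**4. Are foetal and neonatal deaths clearly captured?**
- Not named as outcomes in the Synopsis, in section 4, or among the delivery items in sections 7 and 7.6.4.
- Foetal death in section 9.2 is worded as confirmed by ultrasound. An intrapartum stillbirth may never be confirmed that way, so it is not clearly covered by that criterion.
- Death as a general criterion does not say whether the new-born is included. Section 13.6 gives the new-born its own study number, whereas the initial SAE report in section 9.3 asks for the participant's ID.

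**5. How much calendar time follows the last scheduled safety evaluation?** Inputs: randomisation at 18 weeks (the protocol's upper limit) and Visit 3 at 32 weeks. The week of delivery is not given, so 37 to 42 weeks is assumed.

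Share = (delivery − 32) / (delivery − 18)
- Delivery at 37 weeks: 5/19 = 26%
- Delivery at 40 weeks: 8/22 = 36%
- Delivery at 42 weeks: 10/24 = 42%

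This is a share of time, not of missed events.

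**The case against.** The strongest reply is that section 9 already covers these events. Death is an SAE criterion and is not limited to the mother. Loss of foetal movements is a separate criterion from ultrasound-confirmed foetal death, and important medical events are also included, so an intrapartum stillbirth could enter by several routes. Section 9.3 requires all SAEs to reach the sponsor within 24 hours, related or not, with no stop at week 32, and it provides for autopsy reports. Section 12.1 has the committee assess all deaths. Delivery also collects real safety outcomes: maternal blood pressure, haemorrhage, blood loss, mode of delivery and preterm birth. Pre-eclampsia is an outcome with no stop at week 32.

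Most of this stands, and it rules out several stronger readings that a reader might infer:

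- *That the gravest events are omitted.* They are reportable once detected and classed as SAEs.
- *That the delivery record has no field for them.* The case report form is not shown; only the protocol's item lists can be checked. Section 11.4 does have data collection tools reviewed against the protocol, so an omission there can carry through.
- *That babies who die have no APGAR, weight or length.* A stillborn baby can be weighed and measured, a baby who dies later can have both APGAR scores, and nothing in the protocol excludes these babies.
- *That the last 26% to 42% of the period has no mandatory safety evaluation.* Delivery is a declared safety visit, and one sentence of section 7.6.4 keeps contact with all women.

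What the reply does not meet is detection and classification. Reporting rules act only on events that someone has found and recognised as SAEs. No delivery item prompts that, the contact rule contradicts itself, and the definition leaves intrapartum and new-born deaths open to interpretation. Nor can this be left to the analysis plan, which cannot summarise what was not collected.

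**Conclusion.** The point holds in this form: foetal and neonatal deaths are not excluded, but the protocol does not secure their complete and even capture by arm after week 32, although new-born safety is a stated objective.

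The conclusion rests on the text alone: safety evaluation tied to Visits 1 to 3, no AE/SAE item in section 7.6.4, conflicting statements on contacts and on end of study, a foetal-death criterion worded around ultrasound, an unspecified scope for death, and no named stillbirth or neonatal-death outcome. The 26% to 42% range assumes randomisation at 18 weeks and delivery at 37 to 42 weeks. It indicates how long the ambiguous period lasts, not how many events would be lost, which the protocol gives no basis for estimating. The primary outcome is not affected, because it is measured at 26 to 28 and at 32 weeks.

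**What to change.** 1. Reconcile sections 5, 7.6.4, 7.11, 9 and 11.6 so that one AE/SAE collection window applies to all randomised women, from randomisation through the delivery record, with its end stated.
2. In section 7.6.4, resolve the two contact sentences. If consent-based calls are kept, say that they are additional to the AE/SAE window and do not define it.
3. Add an AE/SAE item at delivery in section 7.6.4 and in Appendix C.
4. Add stillbirth, and neonatal death before discharge, to the new-born outcomes in the Synopsis and section 4. Take them from the delivery records already used, and report them by randomised group beside APGAR, weight and length.
5. In section 9.2, count foetal death however it is confirmed, and state whether death includes the new-born.

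The cost is protocol wording, a few extra electronic case report form fields and somewhat more AE reporting. No visit is added, because section 7.6.4 already has all women delivering in hospital with data collected there.
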